# Study Design

This is a prospective, single blind, randomized controlled trial with three groups. All groups will receive standard 12 week physiotherapy program provided by LS, including a standardized and progressive eccentric training and strengthening program. The first group will receive IMS (detailed below), while the second will receive an equivalent number of sham (superficial non-intramuscular) needling sessions. The third receives the progressive exercise training program alone. Patients will be recruited from the clinical practice of LS and colleagues; additionally, the study will be advertised through LS’s and AS’s contacts in the IMS, UBC, Physiotherapy Association of BC, and Vancouver Coastal Health networks. After providing informed consent and being screened for inclusion/exclusion criteria, diagnosis will be confirmed by physical examination. Inclusion criteria include subjects 19 to 60 years of age, fluent in English, with a 3 month minimum symptom duration, evidence of midportion Achilles tendinopathy on physical examination and tendinosis on ultrasound; and objective signs by Gunn IMS assessment of neuropathic change in the L5-S2 segmental levels including the presence of taut muscle bands amenable to IMS.^49^ Tight bands palpated in muscles paraspinally (dorsal rami) from T1 down and peripherally (ventral rami) from T12 down will also be treated in the IMS group, but participants without findings in the L5-S2 levels will be excluded to limit variability among subjects. Exclusion criteria include IMS contraindications (infection in the area, pregnancy, bleeding disorders, history of bacterial endocarditis, post-surgical implant in last four to six months and major surgery in the last three months), previous treatment with IMS or TCMA (for blinding purposes); true leg length difference of greater than ½” previous corticosteroid injections or recent fluoroquinolone use and systemic inflammatory disease. Those demonstrating the presence of other syndromes that cause pain in and around the Achilles tendon will be excluded by history-taking and physical examination: partial tearing, posterior ankle impingement/ os trigonum syndrome, tenosynovitis, dislocation of the peroneal or other plantar flexor tendons, irritation or neuroma of the sural nerve or insertional Achilles pain. Patients will be randomized by the research assistant ([name]) who is blinded to the patient’s baseline data using a random number generator (SPSS v.16.0).

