**Sham needling**

The appropriate control for acupuncture or needling studies is always controversial, as the act of needling nonspecifically, even superficially, can induce a variety of physiological responses as well as a variable level of placebo response.^63^ Nonetheless, recently the importance of including both sham needling and no-treatment controls has been emphasized (c.f. section 6, and figure 1, in ^63^), and considered superior to non-penetrating “placebo needles.^63^ In the sham needling group, eight acupuncture needles will be inserted into the dermis (1-2 mm) of the buttock, posterior thigh and calf and will be left *in situ* for ten minutes. Points will be chosen that do not mimic either IMS or TCMA techniques. To avoid mimicking IMS treatment the needles will be inserted away from any tight muscle bands that may be present and will be inserted superficially so that no muscle penetration occurs. To avoid mimicking TCMA treatment, meridians in the treatment area and points used to treat heel pain specifically will be avoided, the depth of needle insertion will be superficial, and no “deqi” sensation will be elicited. Meridians in the area of the buttock (the bladder and Du meridians) are in the midline of the buttock and medial to this and so will not correspond with needle points used in IMS (more lateral). In the posterior leg, the bladder meridian is in the midline to the level of the inferior border of the gastrocnemius muscle and so will not correspond with IMS-targeted muscle banding (medial and lateral of the midline). Below the gastrocnemius muscle the bladder meridian moves laterally and so will not correspond with IMS needling of the Achilles tendon itself. No sham needles will be used in the area of the lower back or sacrum as the IMS points and TCMA points correspond more closely in this region. Particular care will be taken to avoid needling in the area of TCMA points used to treat heel pain specifically in the treatment area, these being: Bladder 57 (inferior edge of gastrocnemius muscle in midline) and Bladder 60 (in the depression midway between the lateral malleolus and the Achilles tendon, level with the high point of the bone), Kidney 4 (medial ankle, in the depression anterior to the angle formed by the Achilles tendon and the calcaneum), Gall Bladder 34 - “the physio point” (in the depression anterior and inferior to the head of the fibula) and Bladder 40 (at the mid-point of the transverse crease of the popliteal fossa).^64^

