# Statistical analysis

Based on the published literature, we estimate that the no-needling and sham needling groups will improve on average by 20 VISA-A points after 12 weeks (due to the effects of exercise-based physiotherapy management),^25^ and we hypothesize that the IMS group will improve by a further 15 points (the minimum clinically significant difference).^42^ The SD of a single VISA-A score is 15^67^, and correlation between repeated measurements on the same patient after 1 week is 0.80.^67^ This makes the SD for the difference between 2 measurements on the same patient approximately 9.5. To detect these effects in a one-way ANOVA model with a residual standard deviation of 9.5 with power 95%, a sample size of 11 patients is needed in each group for a total of 33 patients. Assuming a 20% drop-out rate,^43^ 42 patients will initially be recruited and enrolled. The primary analysis will be a one-way Analysis of Variance with the response being the change in patients VISA-A score at 12 weeks. Secondary analyses will be performed on the change in patients VISA-A score at 6 months and 12 months from baseline, and on changes in dorsiflexion range of motion and global improvement scale. Inter-group post-hoc tests will be conducted in consultation with UBC statistical consulting services ([name], manager). Intention to treat analysis will be employed. If a clinically significant effect of IMS in Achilles tendinopathy exists, this pilot study has a 95% chance of successfully detecting it. If there is no clinically significant effect of IMS in Achilles tendinopathy, this study has a 95% chance of reaching this conclusion.

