# Scientific rigor

If the results indicate the existence of a clinically significant effect of IMS, then a larger study with greater attention to mechanisms would be indicated in future. By including both control groups (exercise alone, sham needling), the study design will allow appropriate conclusions to be drawn. If an exercise alone group is not included and if the sham needling and IMS groups were equivalent, then we would not know if IMS and sham needling are equally effective or equally ineffective. Conversely, if we did not have a sham needling group and if the IMS group were superior to exercise group, then we could not conclude that IMS is effective – the effects may have been due to a non-specific effect of needling.^63^ After 50% of the patients, have been enrolled, one researcher (AS) will check the patient baseline data to ensure that the randomized groups are equivalent (in terms of symptom duration, gender, age, baseline VISA-A). If necessary, the subsequent randomization will be weighted in consultation with UBC statistical consulting services. The RCT will be reported and conducted according to the guidelines of the CONSORT (CONsolidated Standards Of Reporting Trials) statement 2010, and ensuring that a score of 10/11 is achieved on the PEDro score (physiotherapy evidence database). It is not possible to blind the treating therapist therefore a score of 11/11 is not possible.

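### The primary three-group F test cannot separate IMS from a general needling effect, yet its 95% power is stated as the chance of detecting an IMS effect

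*Protocol*

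**What the plan says.** The Study Design section describes three arms: IMS, sham needling and exercise alone, all on the same exercise programme. The Statistical analysis section then states: "The primary analysis will be a one-way Analysis of Variance with the response being the change in patients VISA-A score at 12 weeks". No pairwise contrast is named as primary. On pairwise comparisons it says only: "Inter-group post-hoc tests will be conducted in consultation with UBC statistical consulting services".

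The power calculation assumes that "the no-needling and sham needling groups will improve on average by 20 VISA-A points after 12 weeks" and that IMS adds 15 points, which the protocol calls the smallest clinically significant difference. With a residual SD of 9.5 it arrives at 11 per group for 95% power in the ANOVA, and at 42 enrolled after allowing for 20% drop-out. The section closes with two statements about IMS itself: a 95% chance of detecting a clinically significant effect if there is one, and a 95% chance of concluding that there is none if there is none.

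The Scientific rigor section explains the sham arm. Without it, a gain of IMS over exercise could not be credited to IMS, because "the effects may have been due to a non-specific effect of needling". The Sham needling section adds that needling, even superficial, "can induce a variety of physiological responses as well as a variable level of placebo response".

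**The concern.** An F test on three groups rejects whenever any group mean differs from the others. It does not say which one. The sham arm is there to separate a specific IMS effect from a general needling effect, and the F test merges the two. A significant primary result would therefore be compatible with the explanation that the sham arm was added to exclude.

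The possibility is a live one on the protocol's own account. It accepts that superficial needling can produce responses, and its Limitations section says that the size of the placebo response to needling in this condition has not been published. The planning assumption nevertheless sets sham equal to no needling.

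IMS versus sham is also the cleaner comparison. The needling arms have equivalent session numbers and the same rest advice, whereas the Limitations section says that visits and exercise sessions differ somewhat from exercise alone.

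At stake is what counts as a positive trial, and whether the two 95% statements are true of the test they are attached to.

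**Working it through.** **Inputs** (Statistical analysis section): SD of one VISA-A score 15; correlation 0.80; mean changes 20 (exercise), 20 (sham), 35 (IMS); 11 per group. Alpha is not stated. I assume 0.05 two-sided, which reproduces the protocol's sample size.

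**1. The protocol's own figures.**
- SD of change = 15 × √(2 × (1 − 0.80)) = 9.49, stated as 9.5.
- The grand mean is 25, so the squared deviations sum to 25 + 25 + 100 = 150. Noncentrality = n × 150 / 9.5² = 11 × 150 / 90.25 = 18.28, on 2 and 30 df.
- Power of F is 94.2% at 10 per group and 96.2% at 11, so 11 is the smallest number reaching 95%.
- 33 / 0.80 = 41.25, rounded up to 42 for three equal groups.

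The figures reproduce, and they belong to the F test.

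**2. The same test with no IMS effect beyond sham.** Let the mean changes be 20, 35, 35. The grand mean is 30 and the squared deviations sum to 100 + 25 + 25 = 150. The noncentrality is again 18.28, so the power is identical.

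| True mean change: exercise, sham, IMS | F significant | IMS better than sham (unadjusted) |
|---|---|---|
| 20, 20, 35 | 96.2% | 94.8% |
| 20, 35, 35 | 96.2% | 2.5% |

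F is also significant 96.2% of the time if sham alone is 15 points worse (20, 5, 20), since the squared deviations again sum to 150.

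**3. Power for IMS versus sham.** The noncentrality of t is 15 / (9.5 × √(2/11)) = 15 / 4.05 = 3.70.
- With the pooled three-group error (30 df): 94.8%. With a two-sample t test: 94.1%.
- If F must also be significant (400,000 simulated trials): 93.4%.
- With Tukey adjustment: 88.4%.
- IMS better than both controls, if sham equals exercise alone: 90.9% unadjusted, 81.3% with Tukey.

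**4. The statement about concluding no effect.** In the 20, 35, 35 case there is no IMS effect beyond sham, yet the primary test is non-significant in only 100 − 96.2 = 3.8% of trials. The 95% holds for F only when all three means are equal, where it is simply 1 − alpha. Even then, a non-significant test does not by itself establish the absence of a clinically significant effect.

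**The case against.** The strongest reply is that post-hoc tests are the ordinary name for pairwise follow-up to an ANOVA. Three groups have only three pairs, and the choice of method commonly sits in an analysis plan, which is not shown here. With three groups, F followed by unadjusted pairwise tests keeps the family-wise error at 5%. Under that sequence, IMS would be declared better than sham in about 2.5% of trials when the two are equal, not in 96%. The Scientific rigor section suggests that the authors would not stop at F.

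Much of this stands. A reader might infer that the decisive comparison will be picked after seeing the data, but the wording leaves the contrast open and does not show such an intention. What an analysis plan would not cure by choosing a pairwise method is that the protocol has already made F the primary analysis and attached its power to IMS.

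Other stronger readings also fail:
- **Serious underpowering.** A single unadjusted IMS-versus-sham test has about 95% power. The lower figures need a Tukey adjustment that the protocol does not specify and, at 14 per arm with no drop-out, Tukey power for this contrast is 95.5%. A scenario in which sham carries part of a 15-point IMS benefit tests a difference below the protocol's own 15-point minimum, so it does not contradict the power claim.
- **IMS must beat both controls to be called effective.** The Scientific rigor section does not say this. It says that superiority over exercise could not be interpreted without a sham arm.
- **IMS versus exercise should be tested only after IMS beats sham.** That gate would block the comparison when sham and IMS are alike, which is the case for which the protocol keeps the exercise-alone arm: to tell whether both work or neither does.

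**Conclusion.** The point holds in a limited form. The designated primary test cannot distinguish an IMS effect from a general needling effect, and both closing 95% statements are attached to a test that does not address them. The size is plain: F is significant about 96% of the time whether IMS alone, or sham and IMS equally, are 15 points better than exercise alone. This rests on the protocol's SD of 9.5, 11 evaluable patients per arm and an assumed alpha of 0.05. The equal-needling scenario is an illustration, chosen because the protocol itself names that explanation; it is not a forecast.

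The sample size is not in error. It remains adequate for a single IMS-versus-sham contrast under the same inputs: 94.1% to 94.8%, against the stated 95%. The defect lies in which test is called primary and in what the power sentences claim.

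**What to change.** - **Primary contrast.** Name IMS versus sham on 12-week VISA-A change as the single primary contrast, two-sided 5%, with a 95% confidence interval, estimated from the three-group model.
- **Secondary contrasts.** Prespecify IMS versus exercise alone and sham versus exercise alone, reported whatever the primary result. Both are needed: IMS versus sham alone cannot show whether both work or neither does, nor whether sham did worse than exercise alone.
- **Omnibus F.** Report it descriptively.
- **Power.** State about 95% for a 15-point IMS-versus-sham difference at 11 per arm and, if wanted, about 91% for IMS to beat both controls, unadjusted and assuming that sham equals exercise alone. State the alpha.
- **The no-effect sentence.** Delete or reword it. A defensible version is that, if IMS and sham are truly equal, the chance that the 95% interval for their difference lies wholly below 15 points is about 95%. This follows by symmetry from the 94.8% above, since the noncentrality is −3.70 in place of 3.70.

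The cost is a few sentences of protocol text and no extra patients. A significant F, or a gain over exercise alone, would no longer count as primary success.

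### The stated 95% chance of concluding that IMS has no clinically significant effect holds only at a true effect of zero, not for effects up to 15 points

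*Protocol*

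**What the plan says.** All of this is in the protocol's section Statistical analysis.

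- Expected change: "we estimate that the no-needling and sham needling groups will improve on average by 20 VISA-A points after 12 weeks", and "we hypothesize that the IMS group will improve by a further 15 points (the minimum clinically significant difference". The 15 points are therefore both the hypothesised effect and the threshold for clinical significance.
- Variability: the "SD for the difference between 2 measurements on the same patient approximately 9.5".
- Size: "a sample size of 11 patients is needed in each group for a total of 33 patients", for 95% power, with 42 enrolled to allow for 20% drop-out.
- Primary test: "The primary analysis will be a one-way Analysis of Variance with the response being the change in patients VISA-A score at 12 weeks". Post-hoc comparisons between groups are to be settled with statistical consultants.
- The section closes with two claims. The first is a 95% chance of detecting a clinically significant effect if one exists. The second is "If there is no clinically significant effect of IMS in Achilles tendinopathy, this study has a 95% chance of reaching this conclusion".

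The section gives no significance level. It does not say what result would count as reaching the negative conclusion.

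**The concern.** The two closing claims are written as mirror images, but only the first follows from the sample-size calculation. With 15 points as the threshold, no clinically significant effect is a range of true values from zero (or below) up to just under 15. One probability cannot describe that whole range. The ANOVA's null hypothesis is a single point, equal means, and its behaviour there says little about true effects of 5 or 10 points.

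The inference also fails in the other direction. A non-significant test of equal means is not evidence that the effect is below 15.

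The sentence matters because it tells readers how much weight a negative result will bear. The section Scientific rigor ties a larger study to the results indicating a clinically significant effect, and the section Ability to do the work plans prompt dissemination to practitioners. A reader who trusted the sentence could take a non-significant result as strong assurance that IMS does not help, which the design cannot give.

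**Working it through.** **Inputs from the Statistical analysis section.** Mean changes 20, 20 and 20 + d, where d is the true IMS effect; threshold 15; SD of change 9.5; 11 per group; one-way ANOVA with 2 and 30 degrees of freedom.

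**Assumed input.** Alpha is not stated. The smallest group size reaching 95% power at d = 15 is 15 at alpha 0.01, 12 at 0.025, 11 at 0.05 and 9 at 0.10. Of these levels only 0.05 gives the protocol's 11, so 0.05 is used.

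**Reproducing the protocol's own figures.**

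- SD of change: 15 × √(2 × (1 − 0.80)) = 9.49, rounded to 9.5.
- Noncentrality of the F test: λ = n × (2/3) × d² / SD². At d = 15 and n = 11, λ = 11 × (2/3) × 225 / 90.25 = 18.28, which gives power 96.2%. Ten per group gives 94.1%, so 11 is right.
- Drop-out: 33 / 0.8 = 41.25, which becomes 42 with three equal groups of 14.

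**Chance of a non-significant ANOVA.** This is the probability that a noncentral F(2, 30, λ) falls below the critical value 3.316.

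| True effect d | λ | Chance of non-significance |
|---|---|---|
| 0 | 0 | 95.0% |
| 1 | 0.08 | 94.4% |
| 2 | 0.33 | 92.7% |
| 3 | 0.73 | 89.7% |
| 5 | 2.03 | 79.0% |
| 10 | 8.13 | 32.2% |
| 14 | 15.93 | 6.6% |

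With no drop-out (14 per group) the figures at 5 and 10 points fall further, to 73.7% and 20.3%.

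**Does non-significance rule out 15 points?** Suppose the two controls have the same observed mean and the pooled SD is 9.5. The ANOVA is non-significant when the observed IMS difference D satisfies 11 × (2/3) × D² / (2 × 90.25) < 3.316, that is D < 9.03. The 95% half-width against one control is 2.042 × 9.5 × √(2/11) = 2.042 × 4.051 = 8.27. For any D between 15 − 8.27 = 6.73 and 9.03, the ANOVA is non-significant and the interval still contains 15.

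**The more favourable reading.** Suppose the negative conclusion meant that the upper 95% limit for IMS minus control lies below 15. Against one control, the chance is the probability that a noncentral t with 30 df and noncentrality (15 − d) / 4.051 exceeds 2.042. Against both controls it was simulated with 400,000 runs.

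| True effect d | One control | Both controls |
|---|---|---|
| 0 | 94.8% | 91.0% |
| 5 | 66.6% | 52.1% |
| 10 | 22.2% | 10.5% |

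Here too the claimed 95% is met only at about zero effect, and only against a single control.

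**The case against.** The strongest reply is that the protocol never says a non-significant ANOVA is how it would conclude no clinically significant effect. It keeps clinical significance (15 points) apart from the test, and it foresees post-hoc comparisons. A significant ANOVA with an observed difference of 8 points need not be reported as clinically significant. Under a bare rule that the observed difference be below 15, the chance against one control exceeds 95% for true effects up to about 8.3 points. This part stands: the size of the shortfall depends on the rule, and no rule is given. It does not rescue the sentence. The bare rule is not stated either, and it also fails nearer the threshold: at d = 10 it gives 89%. None of the three rules gives 95% across all effects below 15.

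Some stronger readings are tempting but not supported:

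- *The 95% is simply one minus alpha under another name.* This is plausible, but alpha is not stated. The confidence-interval reading also gives about 95% at zero effect, so the origin of the figure is an inference.
- *The claim is badly wrong everywhere above zero.* Under the ANOVA reading the shortfall is slight below about 2 points. It is clear from about 3 points and large from 5.
- *Every non-significant result will be reported as proof of no effect.* No section prescribes that.
- *A larger SD makes matters worse.* That needs a correlation the protocol does not give, and the point does not depend on it.
- *The protocol is at fault for lacking an equivalence rule.* Such a rule may sit in an analysis plan that is not at hand. The fault is the sentence, which a later rule would leave standing.

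**Conclusion.** The sentence claims a property that the design does not have. By the protocol's own definition it covers all true effects below 15 points. The probability it gives is met at zero and falls to 79% at 5 points and 32% at 10 if the conclusion rests on the ANOVA, or to 67% and 22% if it rests on a 95% interval against one control. Separately, a non-significant ANOVA does not show that a 15-point effect is absent.

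These figures rest on the protocol's SD of 9.5 and 11 completers per group, on an assumed alpha of 0.05, and on equal true means in the two control groups. This is an overclaim about interpretation. The sample size reproduces and the primary test can stay as it is.

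**What to change.** Delete the sentence, or replace it with wording such as: *If the three groups have equal mean change, the ANOVA has a 5% chance of a false-positive result (alpha 0.05). A non-significant result does not by itself show that a 15-point effect is absent.* This also puts the significance level on record, which the sponsor should confirm.

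If the sponsor wants to be able to draw a negative conclusion, base it on the upper 95% confidence limit for IMS minus control in 12-week VISA-A change being below 15 points. State whether this applies to sham only or to both controls, since Scientific rigor relies on both. Give the chance of meeting the rule at true differences of 0, 5 and 10: about 95%, 67% and 22% against one control, or about 91%, 52% and 10% against both.

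The cost is protocol wording. No extra patients, data or change of model are needed, because the planned ANOVA already supplies the intervals.
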